**Figure 1 fig1:**
[figure not shown]
Flowchart of the study.

### Participants and recruitment

2.2.

Participants will be recruited from the neurologic care unit. The study will be advertised at the bedside between April 2021 and December 2022. Researchers will select potential candidates by reviewing their medical records in the Computerized Patient Record System (CPRS) and communicate the details of this trial to their families. Following the agreement of the participants’ guardians, a neurologist will review them based on the eligibility criteria. Those who meet the criteria have been invited to join the experiment and must go through a neurological examination before being evaluated for rehabilitation. All study participants must give permission by their family members.

Patients who meet the following criteria will be deemed eligible for the trial: (1) age > 18 years, onset >28 days; (2) patients were assessed by using CRS-R (five times) as DoC (UWS, MCS−, and MCS+); (3) patients had not received central stimulants drugs within 48 h before enrollment; (4) no neuromuscular blockers were applied within 24 h prior to enrollment; and (5) no facial or ear pain, no recent ear-related injuries, no metallic prosthetics, and no pregnancy. Patients who meet the following criteria will be excluded from the trial: (1) personal or familial history of seizures and history of cardiovascular disease, with developmental neurological or psychiatric illness history; (2) untreated brain edema; (3) metal implants in the body; (4) unstable vital signs; and (5) contraindications: such as claustrophobia.

### Sample size

2.3.

The main outcome index of this study is the CRS-R scale score, which is set as a paired experiment count, the sample estimation formula is as follow:
$$n=\frac{{\left(Z_{\alpha /2}+Z_{\beta }\right)}^{2*}\sigma^{2}}{\delta^{2}}$$

According to the results of previous studies (4), the estimated difference standard deviation is 15, and the difference is 10, set two-sided = 0.05, and the grasp degree is 90%. According to the sample size calculation formula, 24 subjects were needed. Considering the loss of visits and refusal, at least 30 subjects were needed. Therefore, 30 *VS*/UWS and MCS patients will be randomly selected for each sample group, with a total sample size of 90.

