### Randomization

2.4.

The study will utilize block randomization. The participants will be classified into either the “MCS group” or the “UWS/*VS* group.” All subjects will be randomly divided into the intervention group and control group in a 1:1:1 ratio. To ensure impartiality, a random number will be used to produce a random allocation order, this task will be handled by a person who is not involved in the trial. The order of random allocation will remain undisclosed to those assessing the outcomes and the statistician. After evaluating the baseline information of the suitable participants, their healthcare personals and therapists (including acupuncturists and cognitive therapists) will not know patients random number assigned.

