### Statistical analysis

2.13.

Main statistical analyses will be performed at the individual and group levels (pre vs. post, treatment vs. sham) (26). To examine the differences between the groups, we shall employ the *t*-test or Mann–Whitney test for continuous variables and the Pearson Chi-squared or Fisher’s exact test for discrete values. If a statistically significant result appears, the inequality factors will be considered as potential confounding factors in the final analysis of effectiveness. To account for any potential external influences, linear models or linear regression will be implemented on continuous dependent variables and logistic regression models on categorical dependent variables. The Chi-square test or Fisher’s exact test will be employed to document and assess unfavorable events (26). We will test outcomes on behavior (diagnosis, CRS-R score) and brain data (MRI/EEG). The proportion of responders and the effect size of treatment (*r*, Cohen’s *d*) will be calculated. We will use *t*-tests, Chi-square tests, ANOVA (for normally distributed data), and Wilcoxon test (for non-ordinal data), and mixed-effect regression models, depending on the tested outcomes. EEG and MRI analysis will be evaluated using SPM12 software^1^ and EEGLAB^2^ implemented in MATLAB 9.5 (MathWorks, Natick, MA, United States), respectively. All other statistical analyses will be conducted in SPSS software (version 25). All data will be adjusted to account for multiple comparisons and considered statistically significant if the value of *p* is lower than 0.05.

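### The 90% power in section 2.3 comes from a one-sample paired formula, so it covers a pre-post change within one arm and not the randomised comparison with sham

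*Protocol article*

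**What the plan says.** Section 2.3 (Sample size) takes the CRS-R score as the main outcome, "which is set as a paired experiment count, the sample estimation formula is as follow": n equals the squared sum of the two normal quantiles, times the variance, divided by the squared difference. The inputs are "the estimated difference standard deviation is 15, and the difference is 10", with "set two-sided = 0.05, and the grasp degree is 90"%. It then states: "According to the sample size calculation formula, 24 subjects were needed". The next step is "Considering the loss of visits and refusal, at least 30 subjects were needed", and 30 "patients will be randomly selected for each sample group, with a total sample size of 90".

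The design described elsewhere is parallel. The abstract and section 2.1 describe three groups: sham at the ear lobe, left-sided stimulation, and left plus right stimulation. Section 2.4 says "All subjects will be randomly divided into the intervention group and control group in a 1:1:1 ratio". Section 2.13 says "Main statistical analyses will be performed at the individual and group levels (pre vs. post, treatment vs. sham"), names two-sample tests for differences between groups, and promises adjustment for multiple comparisons without naming a method. No sample size or power is given anywhere for treatment versus sham.

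**The concern.** A paired formula sizes one group in which each patient serves as his or her own control. The mean change in that group has variance σ²/n. A comparison of mean change between two independent arms has variance 2σ²/n, so for the same difference, SD, alpha and power each arm needs twice as many patients. Section 2.3 uses the one-sample answer as the size of every arm, as if it also served the comparison between arms.

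This matters because a pre-post change within one arm cannot separate the effect of stimulation from spontaneous recovery. Only the comparison with sham uses the randomisation, and the article's first aim is to gauge effectiveness. The 90% is the sole justification offered for 90 patients. A reader who carries it over to the sham comparison would take a null result as stronger evidence of no effect than the design can give.

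**Working it through.** **Inputs from section 2.3:** difference 10, SD of the difference 15 (ratio 10/15 = 0.667), two-sided alpha 0.05, power 90%, 24 before loss, 30 per group. **From section 2.4:** three groups, 1:1:1.

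**Step 1. Reproduce the stated figure.** (1.960 + 1.2816)² × 15² / 10² = 10.507 × 2.25 = 23.64, rounded up to 24. Since 24/0.80 = 30, the allowance corresponds to 20% loss, although the rate is not stated. 30 × 3 = 90. Every stated figure reproduces, so the formula used is not in doubt.

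**Step 2. The same inputs for two independent arms.** Assumption: 10 is the difference between arms in mean CRS-R change, and 15 is the SD of one patient's change. The normal formula gives n per arm = 2 × 23.64 = 47.28, rounded up to 48. By the t distribution, 48 per arm gives 89.8% and 49 gives 90.4%, so 49 evaluable per arm are needed.

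**Step 3. Power of the planned numbers.** Two-sample t-test on change, noncentral t. The standard error is 15 × √(2/n) for one active arm versus sham, and 15 × √(1/(2n) + 1/n) for both active arms pooled versus sham.

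| Contrast, two-sided 0.05 | Evaluable | Standard error | 10 / SE | Power |
|---|---|---|---|---|
| One active arm v sham | 24 v 24 | 4.33 | 2.31 | 61.8% |
| One active arm v sham | 30 v 30 | 3.87 | 2.58 | 71.9% |
| Both active arms v sham | 48 v 24 | 3.75 | 2.67 | 74.9% |
| Both active arms v sham | 60 v 30 | 3.35 | 2.98 | 83.9% |

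The normal approximation gives 63.7% and 73.3% for the single-arm contrast, and 76.0% and 84.6% for the pooled one.

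**Step 4. Detectable difference.** For a single active arm versus sham, 90% power requires a standardised difference of 0.956 with 24 per arm, or 0.851 with 30. Multiplied by 15, these are 14.3 and 12.8 points, against the 10 in section 2.3.

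**Step 5. Multiplicity, as a scenario only.** Section 2.13 names no method. If two contrasts with sham were each tested at 0.025, single-arm power would be 50.2% (24 per arm) or 61.2% (30 per arm).

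**Step 6. Baseline adjustment, as a scenario only.** If 15 is the SD of change and pre and post scores have equal variance and correlation ρ, adjusting for baseline multiplies the variance by (1 + ρ)/2. At an assumed ρ of 0.5 the SD becomes 15 × √0.75 = 12.99. Single-arm power is then 74.2% (24 per arm) or 83.4% (30 per arm), and pooled power is 85.9% (48 v 24) or 92.6% (60 v 30). With 60 v 30, pooled power is 90.9% at ρ = 0.6 and 89.2% at ρ = 0.7. The document gives no correlation, so none of these is the trial's power.

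**The case against.** The strongest defence is that section 2.3 never claims 90% for treatment versus sham. It calls its calculation paired, and section 2.13 lists the pre-post comparison among the main analyses. For that analysis the formula fits and the arithmetic is correct. This stands: the fault is a mismatch between formula and design, not a slip in calculation, and no between-arm power has been misquoted. It does not dispose of the point, because section 2.13 gives treatment versus sham equal place and the only power figure leaves it uncovered.

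Second, 10 and 15 come from earlier work and are not defined for use between arms. This also stands, and every recomputed power is conditional on it. If 15 were instead the SD of the difference between two patients, one from each arm, the per-arm SD would be 15/√2 = 10.6 and 24 per arm would give about 90% (normal approximation). The paired label speaks against that reading, but the text should settle it.

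Third, a reader might infer that every active-versus-sham contrast has only 62 to 72% power. The documents do not support that. Sections 2.1 and 2.4 also speak of a single intervention group against control, so a pooled contrast is a possible reading, and it reaches about 75 to 84%. Nor do they support saying that no analysis could reach 90%. Section 2.13 lists linear and mixed-effect models, and a baseline-adjusted pooled analysis with all 90 patients evaluable could pass 90% at some correlations.

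Fourth, section 2.5 mentions two sessions ten days apart, which might suggest a within-patient design. The abstract and sections 2.1 and 2.4 all place patients in separate randomised groups, so that wording does not justify a paired calculation for the sham comparison.

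Finally, the choice of multiplicity method may properly sit in an analysis plan that is not shown. The 0.025 figures are therefore illustrations, and the point does not depend on them.

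**Conclusion.** The point holds in this form: the 90% in section 2.3 applies to a pre-post change within one arm and does not carry over to the randomised comparison. With 10 taken as the between-arm difference in change, 15 as the SD of change, and an unadjusted t-test at two-sided 0.05, one active arm versus sham has about 62% power with 24 evaluable per arm and 72% with 30. The chance of missing a true 10-point difference is thus about 38% or 28%, not 10%. For that contrast, 90% power needs about twice the 24 evaluable patients per arm that the section plans. Pooling the active arms narrows the gap but does not close it under the same test.

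These sizes rest on the assumed meaning of 10 and 15. Multiplicity adjustment would reduce them; baseline adjustment could raise them, by an amount that cannot be computed without a correlation. The mismatch between formula and design depends on none of these assumptions.

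**What to change.** Keep 30 per arm. In section 2.3:

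- Name the primary active-versus-sham contrast (each active arm separately, or both pooled).
- Replace the paired formula with the two-sample formula for that contrast.
- Say whether 10 and 15 are a between-arm difference in CRS-R change and the SD of change, or something else.
- Restate the power, or the difference detectable with 90% power, at the multiplicity-adjusted alpha and with the analysis model actually used. If the model adjusts for baseline, give the assumed correlation or adjusted SD.

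An example, conditional on the stated inputs: with 30 randomised and 24 evaluable per arm, an unadjusted two-sample t-test of one active arm versus sham at two-sided 0.05 has about 62% power for a 10-point difference in change (SD 15), and 90% power for about 14.3 points.

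The cost is a rewritten paragraph and a less favourable stated power. No extra patients and no change to treatment or assessments are needed.

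### Section 2.3 claims 90% power at an unadjusted two-sided 0.05, while section 2.13 adjusts all results for multiple comparisons and reserves no CRS-R comparison at 0.05

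*Protocol article*

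**What the plan says.** Section 2.3 names the CRS-R score as the main outcome, "which is set as a paired experiment count". Its inputs are that "the estimated difference standard deviation is 15, and the difference is 10", with "set two-sided = 0.05, and the grasp degree is 90" per cent; the last term is evidently power. The result follows: "According to the sample size calculation formula, 24 subjects were needed". An allowance for losses is then added: "Considering the loss of visits and refusal, at least 30 subjects were needed". The 30 is used for each of three groups, 90 in total. Nothing in 2.3 allows for more than one comparison.

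The Randomization section (2.4) states "All subjects will be randomly divided into the intervention group and control group in a 1:1:1 ratio". The Abstract and section 2.1 make clear that the three arms are sham, left-sided stimulation, and left plus right stimulation.

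Section 2.13 plans comparisons before versus after treatment and treatment versus sham. It ends: "All data will be adjusted to account for multiple comparisons and considered statistically significant if the value of" p is below 0.05. It gives no adjustment method, no family of tests, no order of testing, and no exemption for CRS-R.

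**The concern.** With two active arms and one sham arm, comparing each active arm with sham gives two primary contrasts. Left against left plus right would be a third. If results are adjusted over these and then judged at 0.05, each contrast faces a stricter threshold than the one used for sizing, so the 90% is not shown at the threshold the analysis would apply.

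What is at stake is how a negative result is read. A contrast that misses its adjusted threshold, in a trial described as having 90% power, could be taken as evidence that taVNS, or one way of delivering it, does not work. The stated power would not support that reading.

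**Working it through.** **Inputs from 2.3.** Difference δ = 10, SD of the difference σ = 15, two-sided α = 0.05, power 90%, 24 evaluable and 30 randomised per group.

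**Assumptions.** Bonferroni, because 2.13 names no method: α = 0.05/2 = 0.025 for two comparisons, and 0.05/3 = 0.0167 for three. For the between-arm calculation, 15 is taken as the SD in each arm of the quantity compared.

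**1. The plan's own figure.** n = (z₁₋α/₂ + z_power)² × σ²/δ² = (1.960 + 1.282)² × 225/100 = 23.64, so 24. The printed figure reproduces, with the whole 0.05 spent on one comparison. Moving from 24 to 30 matches a 20% loss (24/0.80 = 30), although no rate is stated.

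**2. Sample size on the same formula at adjusted alpha.**
- α = 0.025: (2.241 + 1.282)² × 2.25 = 27.9, so 28 evaluable per group.
- α = 0.0167: (2.394 + 1.282)² × 2.25 = 30.4, so 31 evaluable per group.

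The printed 24 therefore contains no multiplicity allowance.

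**3. Power on the plan's paired formula.** Power = Φ(√n × 10/15 − z₁₋α/₂). For n = 24, √n × 10/15 = 3.266; for n = 30 it is 3.651.

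| α | 24 evaluable | 30 evaluable |
|---|---|---|
| 0.05 | Φ(3.266 − 1.960) = 90.4% | 95.5% |
| 0.025 | Φ(3.266 − 2.241) = 84.7% | Φ(3.651 − 2.241) = 92.1% |
| 0.0167 | Φ(3.266 − 2.394) = 80.8% | Φ(3.651 − 2.394) = 89.6% |

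With the noncentral t distribution the figures at 24 are 87.8%, 80.1% and 74.7%; at 30 they are 94.2%, 89.4% and 85.9%. A Dunnett adjustment for two arms against a control (per-comparison α about 0.027) gives 85.4% at 24 on the plan's formula, so a milder adjustment does not close the gap.

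**4. Power for the contrast that is adjusted.** The multiplicity arises from comparisons between arms, whereas the formula in 2.3 is for within-patient differences. For a two-sample t-test with δ/σ = 10/15 = 0.667, the noncentrality is 0.667 × √(n/2): 2.309 at 24 per arm and 2.582 at 30 per arm. Noncentral t power:

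| α | 24 per arm | 30 per arm |
|---|---|---|
| 0.05 | 61.8% | 71.9% |
| 0.025 | 50.2% | 61.2% |

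Adjusting for two comparisons costs 11.6 points at 24 per arm (61.8 − 50.2) and 10.7 points at 30 (71.9 − 61.2). This comes on top of a larger loss from using a paired formula for a comparison between parallel arms.

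**The case against.** The strongest reply is that a stricter threshold does not follow from 2.13. Some procedures adjust for multiplicity and still test a key comparison at the full 0.05. A fixed sequence does so for its first test. With exactly three groups, an overall ANOVA at 0.05 (ANOVA is listed in 2.13) followed by pairwise tests at 0.05 also controls the familywise error. A single contrast of the pooled active arms against sham is not ruled out either, since 2.1 and 2.4 speak of an intervention group and a control group. Details of method and family are commonly left to an analysis plan that is not shown, so their absence is no error here.

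This stands as a limit on the claim. A reader might infer that the analysis will certainly use 0.025 or less and that the 90% is therefore simply false. The documents do not support that, because they do not fix the procedure. What they do contain is a general commitment to adjust, with no order or exemption, beside a sizing that has no adjustment.

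A reader might also take 84.7% or 80.8% as the power of the active-versus-sham comparisons. That is not supported either: those figures apply an alpha split over between-arm tests to a paired, one-sample formula. They show only that the mismatch remains when the plan's formula is accepted. The between-arm power is in step 4.

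Finally, on the plan's own formula 30 evaluable patients per group still give 92.1% or 89.6%. That is correct, but 2.3 sets the extra six per group aside for losses and refusals, so they cannot also be counted on to pay for multiplicity.

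**Conclusion.** The concern holds as an inconsistency between 2.3 and 2.13. The arithmetic in 2.3 is right for one comparison at 0.05; the fault is that the alpha used for sizing is not reconciled with the stated analysis rule.

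Under Bonferroni over two or three comparisons, the stated 90% becomes 84.7% or 80.8% on the plan's formula once the allowed-for losses occur. For the two-sample contrast at 0.025 it is about 50% to 61%. These sizes depend on the assumed method and family: adjustment over more tests would cost more, and a sequential procedure less for its first test. The paired formula is the larger, separate problem, and correcting alpha alone would not restore power for active versus sham. The point deserves correction because it affects the stated power for the primary outcome and is cheap to put right.

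**What to change.** Keep 30 per arm and do one of the following.

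- **(a) In 2.13**, fix before unblinding a hierarchical order for the two active-versus-sham CRS-R comparisons, so that the first is tested at the full 0.05 and the second only if the first succeeds.
- **(b) In 2.3**, restate the power at the per-comparison alpha that 2.13 implies: 0.025 if the family is the two active-versus-sham comparisons. Name that family and the method.

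In either case, give the restated power for the two-sample active-versus-sham contrast at 24 evaluable and at 30 randomised per arm. With the plan's difference and SD this is 61.8% and 71.9% for the first comparison under (a), and 50.2% and 61.2% for each comparison under (b). Do not only change alpha in the paired formula: 2.3 would then print 84.7% to 92.1% for contrasts whose two-sample power is 50.2% to 61.2%.

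The cost is a sentence or two and a less favourable stated power, with no extra patients or procedures. Option (a) has a small downside: the second comparison can be claimed only if the first succeeds.

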### Randomization

2.4.

The study will utilize block randomization. The participants will be classified into either the “MCS group” or the “UWS/*VS* group.” All subjects will be randomly divided into the intervention group and control group in a 1:1:1 ratio. To ensure impartiality, a random number will be used to produce a random allocation order, this task will be handled by a person who is not involved in the trial. The order of random allocation will remain undisclosed to those assessing the outcomes and the statistician. After evaluating the baseline information of the suitable participants, their healthcare personals and therapists (including acupuncturists and cognitive therapists) will not know patients random number assigned.

### Trail protocol

2.5.

Ninety patients will undergo two sessions 10 days apart, with CRS-R and EEG performed before and after VNS. The active session will stimulate the left or right cymba conchae and inner tragus (TENS-200A, SN number: E200A16A000144, the B mode type; stimulation parameters: output pulse width degree of 200us, 20 Hz output 7 s, 4 Hz output, and 3 s alternate cycle output). The taVNS stimulator will be monitored according to patients’ response. The sham stimulation will be applied over the earlobe. We expect behavioral and EEG metrics to be improved in a majority of patients (See Figure 2).

**Figure 2 fig2:**
[figure not shown]
The taVNS stimulation protocol.

### Follow-up

2.6.

The clinical trial concluded 3 months ago and since then, behavioral scale data have been gathered at regular intervals of 3, 6, and 12 months. For eligible subjects, the MRI/EEG will be performed, and blood samples will be collected for target protein determination.

### Blinding

2.7.

The trial has been designed to be double-blind; thus, an external party that is unaffiliated with the experiment will monitor and oversee the execution of the blinding protocol, with the random numbers placed in a sealed envelope. Evaluators are not involved in the process of recruiting and managing patients, while other investigators, operators, and statisticians act on their own. Prior to the conclusion of the statistical analysis, unblinding is done to counteract the analyst’s potential subjectivity in data analysis; meantime, the analyst knew that the patients have been split into three groups, but was unaware of which one is the intervention group. Following the statistical study, the second step of unblinding is executed to identify which group is the treatment group.

### Ethics issues

2.8.

The Ethics Committee of Hangzhou Normal University [NO: (20190083)] and Shanghai Yongci Hospital [No: (YCYY-20211021-003) have both given the green light for the study protocol and consent forms, respectively]. We will ensure that we have the approval of family members of subjects before proceeding.

